### 2.6 Exclusion criteria

1. Patients with severe diseases in important organs, including abnormal liver function, renal failure, heart failure, stroke, and malignant tumors.2. Participated in other clinical trials within 3 months before enrollment.3. Allergic to known drugs or experimental drugs.4. Pregnant and lactating women.5. Obvious mental disorders.

### 2.7 Handling of withdrawal and data management

Participants can withdraw from the study at any time. If any participant stops using study medication or takes other medications that may affect the results during the study, the participant will not be a part of the study anymore. Participants failed to follow up and ones withdrawn from the study were recorded and reported. Incomplete data will be cleaned up if less than 5–10% of participants withdraw from the study. Missing data will be processed through data imputation, intention to treat analysis, and sensitivity analysis if greater than 10% participants withdraw from the study.

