### 2.15 Adverse events

Every adverse event (AE) was recorded, including the start date, end date, degree, relationship between the study drug and AE, and whether the participant is still involved in the study. Any serious adverse event (SAE) was reported to the Research Ethics Committee (REC) within 24 h. If any AE happened on any participant, the researcher asked the participant to stop using the washing decoction and determine if the event is related to the study drug formulation. If necessary, researchers took emergency safety measures to protect the participant from direct harm. If AE persisted, we followed it up until it was resolved. The AE in this study does not include complications clearly related to anal fistula, such as necrosis, prolonged healing, discharge, infection, pain, and itching.

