### 2.17 Data and sample collection

Three study members were trained to master the criteria and methods of case collection to minimize the selection bias. During data collection, the medication of participants was recorded in detail, and the interference and contamination factors in the statistical analysis were excluded.

On the consent form, the participants were asked if they agreed with the use of their data or they chose to withdraw from the trial. This trial does involve collecting biological specimens for storage. All samples were destructed after use.

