### 2.18 Data management and monitoring

An independent Data and Safety Monitoring Board has been established to monitor the conduct and safety of the study. Two members of the research group (YH and XZ) entered the collected information into the Chinese Clinical Trial Management Public Platform under a confidential condition. The hard copy records were preserved at a locked office. No one will be able to change or use the hard copy and electronic data without the authorization of our group.

The investigators did their best to avoid missing clinical trial data. In the process of dealing with missing data, we chose different processing methods, according to the judgment of data managers on the mechanism of missing data. At the same time, it is necessary to make a sensitivity analysis of the test results.

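### Section 2.7 removes randomised participants who stop the wash or take other medication, and names intention to treat only above 10% withdrawal, so the comparison is open to bias from post-randomisation exclusion

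*Protocol article*

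**What the plan says.** All references are to the protocol article.

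- **Removal (2.7).** The rule covers anyone who "stops using study medication or takes other medications that may affect the results during the study, the participant will not be a part" (that is, participation ends). The medications meant are not listed.
- **Low withdrawal (2.7).** "Incomplete data will be cleaned up if less than 5–10% of participants withdraw from the study". The term for what is done to the data is not defined.
- **High withdrawal (2.7).** "Missing data will be processed through data imputation, intention to treat analysis, and sensitivity analysis if greater than 10% participants withdraw from the study".
- **Adverse events (2.15).** "If any AE happened on any participant, the researcher asked the participant to stop using the washing decoction"; relatedness is then assessed. The same section limits this: "The AE in this study does not include complications clearly related to anal fistula". It also has the AE record state "whether the participant is still involved in the study", and it follows persisting events to resolution.
- **Data collection (2.17).** Medication is recorded, and "the interference and contamination factors in the statistical analysis were excluded".
- **Missing data (2.18).** The method is chosen "according to the judgment of data managers on the mechanism of missing data", and a sensitivity analysis is required with no withdrawal threshold.
- **Planned loss (2.16).** 20% of 60 participants, 30 per arm.

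**The concern.** A randomised comparison is protected because the groups analysed are the groups that chance formed. Section 2.7 gives that up for participants selected by what happens to them after randomisation. Stopping the wash can depend on how it is tolerated. Needing other treatment can depend on how the wound is doing. Either may differ by arm, and either may be related to healing, which is a primary outcome.

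Two features make this worse. First, whether an intention-to-treat analysis is done at all depends on an observed withdrawal rate, so the analysis set is not fixed in advance. Second, removal ends participation and not only treatment. The plan makes no provision for later outcome data from these participants, so an analysis plan written afterwards could not recover them.

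**Working it through.** **1. The thresholds as counts.** With 60 randomised, 5% is 0.05 × 60 = 3, 10% is 0.10 × 60 = 6, and the planned 20% loss is 0.20 × 60 = 12.

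| Withdrawals | Rule in section 2.7 |
|---|---|
| 0 to 2 | low-withdrawal rule |
| 3 to 5 | unclear: the limit is a range, not a number |
| exactly 6 | neither rule: not below 10%, not above it |
| 7 or more | imputation, intention to treat, sensitivity analysis |

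Section 2.18 does not fit this table. It leaves the method to judgement and requires a sensitivity analysis at any rate of withdrawal.

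**2. From adverse event to removal.** Section 2.15 leads from an event to a request to stop the wash. Section 2.7 leads from stopping to removal. Joining the two is an inference, since no sentence states the whole chain.

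**3. How much exclusion could matter.** The document gives no figure, so these are assumed scenarios: 30 per arm, normal outcome, no true effect, removed participants drawn at random from the worst-healing 40% of their arm, their data dropped, and a two-sided t-test at 0.05 on those retained.

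The mean of the lowest 40% of a standard normal is −φ(−0.253)/0.40 = −0.386/0.40 = −0.966. Removing k of 30 therefore raises the retained mean by about 0.966k/(30 − k) SD:

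- 6 vs 0: 0.966 × 6/24 = 0.24
- 5 vs 0: 0.966 × 5/25 = 0.19
- 4 vs 1: 0.966 × 4/26 − 0.966 × 1/29 = 0.149 − 0.033 = 0.12
- 3 vs 1: 0.966 × 3/27 − 0.033 = 0.107 − 0.033 = 0.07

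Simulation with fixed counts agrees:

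| Removed, by arm | Share of 60 | Shift (SD) | Type I error |
|---|---|---|---|
| 6 vs 0 | 10.0% | 0.24 | about 13–14% |
| 5 vs 0 | 8.3% | 0.19 | about 10–11% |
| 4 vs 1 | 8.3% | 0.11 | about 6–7% |
| 3 vs 1 | 6.7% | 0.07 | about 5% |

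**4. Sensitivity to the assumption.** For 6 removed from one arm only: if they are exactly the 6 worst outcomes, the shift is 0.34 SD and type I error about 28%; if removal correlates 0.5 with outcome, 0.17 SD and about 10%; if removal is random, type I error stays at about 5%. Equal removal from both arms by the same mechanism gives no shift.

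**5. In outcome units.** The planning SDs in section 2.16 pool to √((2.29² + 2.67²)/2) = 2.487. A shift of 0.24 SD is 0.24 × 2.487 = 0.60 percentage points of wound healing rate, against a planned difference of 33.35 − 27.33 = 6.02.

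**The case against.** The best defence is that the plan expects 20% loss, or 12 participants, and at that rate section 2.7 does invoke intention to treat. Exclusion without it arises only if retention is better than expected. This is correct and narrows the point. It does not remove it, because participants who have been removed have no later outcomes. The intention-to-treat analysis would then rest on imputing cases that may be missing for reasons linked to outcome.

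Several stronger readings are tempting and are not supported:

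- **That every adverse event means removal.** Section 2.15 records whether the participant remains involved, so some may stay. Complications clearly related to the fistula are not counted as adverse events, so poor healing as such does not enter by this route.
- **That safety follow-up is lost.** Section 2.15 follows persisting events until they resolve, and section 2.7 records and reports those withdrawn.
- **That adjusting antibiotics or glucose-lowering drugs triggers removal.** Section 2.8 makes these part of standard treatment in both arms and allows adjustment. Medication outside that standard care is at least as natural a reading of section 2.7. Because the medications are not listed, the other reading remains possible and no more than that.
- **That section 2.17 excludes participants.** It speaks of factors, and what is excluded is unclear.
- **That larger imbalances, such as 9 or 12 removals in total, show the plan's error rate.** Above 6 withdrawals the plan does not rely on dropping participants, so such scenarios do not describe it.

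It is also fair that the choice of imputation method or model can be left to a statistical analysis plan. Who stays under observation, and who is in the primary analysis set, cannot be left so late: the protocol has already stated rules on both, and they conflict.

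**Conclusion.** The point holds as a risk of bias built into the stated rules. A reader might infer that the comparison is biased; the document does not support that, because the number of removals, their split by arm and their relation to outcome are all unknown.

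Where section 2.7 does not clearly call for intention to treat (6 withdrawals or fewer), the inflation is material mainly when nearly all removals fall in one arm: about 10–14% type I error for 5 or 6 vs 0, and close to nominal for 3 vs 1. This assumes removal from the worst-healing 40% and takes the low-withdrawal rule to mean deletion. The shift is small beside the 6.02-point difference assumed for planning, so it matters most if the true effect is absent or modest. Above 6 withdrawals, the weakness is reliance on imputation for outcomes that the plan does not provide for collecting.

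Independently of any scenario, sections 2.7 and 2.18 give different missing-data rules, and section 2.7 has no single lower threshold and no rule at exactly 10%.

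**What to change.** Reconcile sections 2.7, 2.15, 2.17 and 2.18 as follows:

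1. Separate stopping the wash from leaving the study. Participants who stop, or who take other medication, keep their scheduled assessments unless they withdraw consent.
2. Make the primary analysis all randomised participants in the assigned arm, whatever the withdrawal rate.
3. Delete the 5–10% and 10% thresholds and the undefined low-withdrawal rule. State what section 2.17 excludes, or delete that clause.
4. Replace the choice by data managers in section 2.18 with a method and sensitivity analysis fixed before unblinding. The particular imputation or mixed model may be left to the statistical analysis plan.
5. Keep the exclusion as now written only as a per-protocol sensitivity analysis.

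When treatment should be stopped is a clinical matter and is not addressed here.

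The cost is protocol wording, plus already-scheduled visits for a few participants who are off treatment. If some follow-up has already ended, outcomes not collected cannot be recovered, but items 2 to 5 can still be settled before unblinding.

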### 2.8 Interventions

All participants went through an interview to know more information about this study. After obtaining informed consent and completing baseline assessments, eligible participants were randomized to the intervention and placebo groups. Participants were not allowed to take any other Chinese herbal decoction or Chinese patent medicine during the study.

Both groups received standard treatments, including health knowledge education regarding diabetes and anal fistula, formulations of recipes, and taking hypoglycemic, antihypertensive, hypolipidemic, and anti-infective drugs. A personalized treatment plan was formulated after consultation with an endocrinologist, and the plan was evaluated and adjusted throughout the process. The wound surface was routinely cleaned with povidone-iodine after daily defecation. The intervention group was given TCM external washing decoction, JSD (Figure 2), and the information of its constituent botanical drugs is shown in Table 1. The JSD decoction was prepared by the Department of Pharmacy, Hospital of Chengdu University of Traditional Chinese Medicine. The specific steps are as follows: (1) Bai Zhi, Zi Cao, and Dang Gui are added to 500 ml of water and soaked for 30 min, and the mixture of water and herbs is transferred to the decoction machine, boiled at high heat to 100°C under standard atmospheric pressure (the boiling time to 100°C should not be more than 5 min), turned to low heat and maintained the temperature constant at 85°C–95°C, then continued to decoct for 30 min, obtained 200 ml of the botanical drug liquid was filtered, and set aside. (2) A measure of 500 ml of water is added again, boiled to 100°C on high heat (boiling time to 100°C should not be more than 5min), turned down the heat and maintained the temperature constant at 85°C–95°C, and decocted for 45 min. (3) The liquid from the previous two steps are mixed to obtain a total of 400 ml of the liquid (liquid 1). (4) Grind Ru Xiang, Mo Yao, and Er Cha, in advance, are filtered through a 2-mm sieve, 400 ml of water is added, boiled in high heat to 100°C (boiling time to 100°C should not be longer than 5 min), turned down the heat and maintained the temperature constant at 85°C–95°C, added pre-ground Xue Jie and Bing Pian (filtered through 2 mm sieve) at the 14th min, continued to boil for 2 min to get 200 ml of the liquid (liquid 2). (5) Liquid 1 and liquid 2 are mixed thoroughly to get 600 ml of liquid. (6) After waiting for its temperature to 35°C–40°C, 200-ml herbal medicine bags are plasticized. The decoction was produced in the same batch as far as possible and quality-checked by the manufacturer. To ensure that the decoction is not contaminated, the decoction vessels and filtration and dispensing equipment were completely cleaned in advance to make sure there were no residuals.

**FIGURE 2 F2:**
[figure not shown]
Jiedu Shengji decoction (JSD).

**TABLE 1 T1:** Components of JSD.

Name of the drug	Use part	Manufacturer	Dose (g)	Method of use	Dosage form, dosage, frequency, and duration of treatment	Registration or not (Y/N)	Quality control report? (Y/N)	Storage condition
Zi Cao [*Arnebia euchroma* (Royle) Johnst.]	Whole plants	Sichuan Chinese Herb Preparation Co., Ltd., Sichuan, China	15	Washing and sitz bath for 30 min	Liquid, 200 ml, once a day, last 4 weeks	Y-registered in relevant administration	Y-prepared according to the manufacturer	The drugs are sealed and stored in a Chinese medicine warehouse at 0–30°C and 45–75% humidity
Dang Gui [*Angelica sinensis* (Oliv.) Diels.]	Roots	Sichuan Chinese Herb Preparation Co., Ltd., Sichuan, China	20	Washing and sitz bath for 30 min	Liquid, 200ml, once a day, last 4 weeks	Y-registered in relevant administration	Y-prepared according to the manufacturer	The drugs are sealed and stored in a Chinese medicine warehouse at 0–30°C and 45–75% humidity
Ru Xiang [*Boswellia carterii* birdw.]	Resin	Sichuan Chinese Herb Preparation Co., Ltd., Sichuan, China	15	Washing and sitz bath for 30 min	Liquid, 200ml, once a day, last 4 weeks	Y-registered in relevant administration	Y-prepared according to the manufacturer	The drugs are sealed and stored in a Chinese medicine warehouse at 0–30°C and 45–75% humidity
Mo Yao [*Commiphora myrrha* (T.Nees) Engl.]	Resin	Sichuan Chinese Herb Preparation Co., Ltd., Sichuan, China	15	Washing and sitz bath for 30 min	Liquid, 200 ml, once a day, last 4 weeks	Y-registered in relevant administration	Y-prepared according to the manufacturer	The drugs are sealed and stored in a Chinese medicine warehouse at 0–30°C and 45–75% humidity
Xue Jie [*Daemonorops draco* (Willd.) Blume]	Resin	Sichuan Chinese Herb Preparation Co., Ltd., Sichuan, China	15	Washing and sitz bath for 30 min	Liquid, 200ml, once a day, last 4 weeks	Y-registered in relevant administration	Y-prepared according to the manufacturer	The drugs are sealed and stored in a Chinese medicine warehouse at 0–30°C and 45–75% humidity
Bing Pian [*Cinnamomum camphora* (L.) J.Presl]	Extract	Sichuan Chinese Herb Preparation Co., Ltd., Sichuan, China	5	Washing and sitz bath for 30 min	Liquid, 200 ml, once a day, last 4 weeks	Y-registered in relevant administration	Y-prepared according to the manufacturer	The drugs are sealed and stored in a Chinese medicine warehouse at 0–30°C and 45–75% humidity
Bai Zhi [*Angelica dahurica* (Hoffm.) Benth. Et] Hook. f. ex Franch. et Sav]	Roots	Sichuan Chinese Herb Preparation Co., Ltd., Sichuan, China	20	Washing and sitz bath for 30 min	Liquid, 200ml, once a day, last 4 weeks	Y-registered in relevant administration	Y-prepared according to the manufacturer	The drugs are sealed and stored in a Chinese medicine warehouse at 0–30°C and 45–75% humidity
Ercha [*Acacia catechu* (L. F.) Willd]	Dry extract of skin, branch, and stem	Sichuan Chinese Herb Preparation Co., Ltd., Sichuan, China	20	Washing and sitz bath for 30 min	Liquid, 200ml, once a day, last 4 weeks	Y-registered in relevant administration	Y-prepared according to the manufacturer	The drugs are sealed and stored in a Chinese medicine warehouse at 0–30°C and 45–75% humidity

The placebo group was given placebos made of excipients and flavoring agents. Placebo formula: pyrosyrup (edible), apple green (edible), and lactose (medicinal). Placebos were packaged, shaped, and colored to be the same as JSD. Placebos were produced by the Placebo Experimental Center of School of Pharmacy, Chengdu University of Traditional Chinese Medicine, which had no efficacy or side effects. The external washing decoction was placed in a special vessel and air-dried to lukewarm for patients to take sitz bath for 30 min/time. Then, the bases of incisions were packed outward along with a gauze in moderate tightness. The incisions were covered with sterile gauze and fixed with adhesive plaster. The wound dressing was changed once a day for 4 weeks. We followed up the participants at the 8th, 12^th^, and 16th weeks after the dressing change was finished to record and analyze the recurrence.

### 2.9 Randomization and allocation concealment

Randomization was performed by an independent statistician ([name]). Random sequences were generated by BMI SPSS Statistics 24.0 software. Given the number of seeds, 60 participants were randomly assigned to the intervention and placebo groups. The random distribution table was determined in triplicate, with one copy for the project leader (KJ), one for the pharmacist (TX), and another one for the statistician ([name]).

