### 2.10 Blinding

This study is designed to be a double-blind trial. During the experiment, neither participants nor researchers had group information. The medication number, label, and packaging for each participant were prepared from 001 to 030. Random numbers were sealed in double opaque envelopes, which were kept by [name], who was responsible for the blind method management. Every participant received their corresponding emergency letters, which were kept until the end of the trial.

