### 2.16 Sample size

According to the sample size estimation method for the comparison of two sample means, we preset the sample size of the placebo group and the intervention group for them to be equal. The calculation formula is as follows:
$$n=2\sigma^{2}\times \frac{f\left(\alpha ,\beta \right)}{{\left(\mu_{1}-\mu_{2}\right)}^{2}},$$

where *n* represents the overall sample size of the study, μ1 and μ2 are the mean values of the control group and the test group, respectively, and σ is the standard deviation. We set that the probability of making type I error in this study shall not be greater than 5%, and the probability of making type II error at the same time shall not be greater than 10%, that is, α = 0.05 and β = 0.1. Referring to Chinese literature reports on TCM external washing for the treatment of postoperative wound of anal fistula, the wound healing rate (%) in literatures was set as the clinical efficacy observation, the mean value was 33.35, and the standard deviation was 2.29 in the intervention group, and the mean value was 27.33 and the standard deviation was 2.67 in the placebo group. The estimated loss of the follow-up rate was 20%, so the total study sample size was 60, of which 30 was for the intervention group and 30 was for the placebo group.

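### Concealment and blinding are described in contradictory terms and are not assured: the project leader is given the allocation table, and medication numbers 001–030 cannot uniquely identify 60 participants

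*Protocol article*

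**What the plan says.** Section 2.9 has an independent statistician perform the randomisation, in which "60 participants were randomly assigned to the intervention and placebo groups". Of the resulting table it says: "The random distribution table was determined in triplicate, with one copy for the project leader". The pharmacist and the statistician hold the other two copies. The section does not say whether any copy is sealed or coded.

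Section 2.10 makes four statements that bear on the same matter:

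- On knowledge of allocation: "During the experiment, neither participants nor researchers had group information".
- On pack identity: "The medication number, label, and packaging for each participant were prepared from 001 to 030".
- On concealment: "Random numbers were sealed in double opaque envelopes", kept by the person who manages the blind.
- On code-breaking: "Every participant received their corresponding emergency letters, which were kept until the end of the trial".

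Section 2.16 fixes the arm sizes: "the total study sample size was 60, of which 30 was for the intervention group and 30 was for the placebo group". Section 2.3 gives recruitment to three team members and assignment to two others. Section 2.8 says that the placebo matched the decoction in packaging, shape and colour.

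**The concern.** Three statements on who can learn the allocation, and how, do not fit together.

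1. A project leader who holds the allocation table has group information, unless the copy is sealed or coded. That contradicts the statement that researchers had none. The leader is not peripheral to the trial: under section 3.2 this person, with the supervisor, agrees any change to the programme.
2. A number meant for each participant must be unique. A range of 30 does not provide that for 60 people.
3. The emergency-letter sentence leaves open who physically holds the letters.

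The stakes come from the outcomes in section 2.12.1. Secretion, oedema and granulation colour are scored by eye. Pain is reported by the patient on a visual analogue scale. Healing time depends on someone deciding when epithelialisation is complete, and the healing rate uses a measured length and width. Measures of this kind can shift when the rater or the patient knows the arm. Other decisions also need a blind decision-maker: removing participants who take other medication (section 2.7), judging whether an adverse event is drug-related (section 2.15), and choosing how to handle missing data (section 2.18). The introduction presents double-blinding as the advance over the earlier single-centre study, so the trial's own rationale depends on it.

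**Working it through.** **Pack numbers**

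Inputs: 60 randomised (section 2.9); 30 per arm (section 2.16); numbers 001 to 030 (section 2.10); three hospitals (section 2.2).

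- The plan's own total: 30 + 30 = 60 participants. This agrees between sections 2.9 and 2.16.
- Distinct medication numbers: 030 − 001 + 1 = 30.
- If each participant has a unique number: 60 − 30 = 30 participants have none, which is half the trial.
- If the range is used once in each arm: 2 × 30 = 60 packs, which matches the total, but every number occurs twice. The number alone then does not say which of two packs is meant. Something else must tell them apart, and the article does not say what.
- If the range restarts at each hospital: 3 × 30 = 90 packs, which does not match 60.
- Unique numbering needs 060 − 001 + 1 = 60 numbers, that is, 30 more than stated.

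No reading of 001–030 gives 60 participants one unique number each. The once-per-arm reading is the only one of these that yields 60 packs. It carries a conditional risk: if a visible mark, even a neutral one such as A and B, separates the two series, the mark is a two-group code. In a two-arm trial, learning what one series contains then reveals the arm of all 60 participants, not only of the 30 in that series.

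**Allocation table**

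No arithmetic applies, so the statements are set side by side.

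- Section 2.9: the project leader has a copy of the table.
- Section 2.10: researchers have no group information.

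Both can be true only if the copy is sealed or coded, or if the leader is not counted among the researchers and takes no part in enrolment, care or assessment. The article states none of these. The pharmacist's and the statistician's copies are a different matter: holding the list in those roles does not in itself break the blind. No reason is given for the leader to hold one.

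**Emergency letters**

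The sentence in section 2.10 has two readings: each participant was handed a letter, or each participant had a corresponding letter that staff retained. The contents are not described. Only the first reading, together with a letter that carries the treatment code, puts the code in the participant's hands.

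**The case against.** The strongest reply is that several safeguards are stated and that nothing shows a breach. An independent statistician randomised, opaque envelopes were kept by a person assigned to manage the blind, recruiters and assigners were different people, and the placebo was matched in packaging, shape and colour. The initials visible in section 2.3 are not the project leader's, and nowhere is the leader said to enrol, treat or score patients. Whether the leader's copy was sealed is a detail that a fuller protocol might hold. Finally, 001–030 equals one arm exactly, so it may describe numbering within each arm, or be a slip for 060.

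Most of this stands. A reader might infer that the trial is neither concealed nor double-blind. The documents do not support that, because the safeguards above are part of the stated design. A reader might also infer that only 30 packs exist, that the packs form two visibly different series, or that participants carry their own codes. Each is one possible reading, not a stated fact.

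What the reply does not do is remove the contradictions. None of the safeguards explains the leader's copy or makes 30 numbers unique for 60 people. One recruiter's name is removed from the text, so overlap with the leader can be neither asserted nor excluded. The point also does not rest on missing detail: the article states both sides of the conflict itself.

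**Conclusion.** The point holds as a contradiction in the stated procedures: concealment and blinding are not assured as written. Sections 2.9 and 2.10 conflict on whether the project leader has group information. The number range covers 30 of 60 participants if numbers are unique, or repeats every number twice if it runs once per arm. The emergency-letter wording is an ambiguity to be resolved. It becomes a threat to the blind only if participants held the letters and the letters carry the code.

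The conclusion assumes that the leader's copy was readable, because no sealing or coding is stated. If it was sealed and never opened, the first conflict disappears once the text says so. The size of any bias cannot be calculated from the documents. What makes the point worth correcting is that most of the wound-healing measures in section 2.12.1 depend on human judgement.

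**What to change.** 1. Restrict the unblinded table to the independent statistician and the pharmacist until database lock. If the leader's copy was in fact sealed, say so and log any opening.
2. Number packs uniquely from 001 to 060 in random order, so that number and arm are unrelated.
3. Keep the emergency code-break letters with the pharmacist or the site, with every opening logged, and reword the sentence in section 2.10 to match.
4. For participants already enrolled, report who had access to the table and whether any of those people enrolled or assessed participants. Qualify the double-blind claim accordingly.

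The cost is a short amendment reconciling sections 2.9 and 2.10, plus relabelling of any packs not yet dispensed. Recruitment began in June 2022 and was expected to finish in December 2022 (section 3.1), so there may be few or no packs left to relabel. In that case item 4, with a plain account of how the 60 packs were actually identified, is the part that still matters.
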